### Objectives

The aim of the study is to assess the effects of different medical treatment modalities for T2DM, separately and combined in community dwelling older subjects, on metabolic, functional and anthropometric parameters.

#### Primary aims and hypotheses

##### Aim

To evaluate the short-term efficacy (10–20 weeks) of CRT, a V-Med diet separately or in combination with CRT, or empagliflozin separately or in combination with CRT, on the body weight, body composition and functional status in community dwelling older subjects with T2DM.

##### Hypothesis 1

We expect that the increase in lean body mass (LBM) will be superior in the CRT arm vs. the other groups after 10 weeks. After 20 weeks the relative increase in LBM will be higher in the V-Med diet + CRT compared to the empagliflozin + CRT group.

##### Hypothesis 2

We expect that the functional status would improve the most in the CRT arm vs. the other groups after 10 weeks. After 20 weeks, functional improvement will be larger in the combined therapy of V-Med diet + CRT as compared to the empagliflozin + CRT combination.

#### Specific secondary aims

To profile community dwelling older people with T2DM in terms of overall health status, body composition, physical and metabolic function.To evaluate the effects of the three study arms on glycemic control, insulin resistance, hormonal and lipid profiles, blood pressure and energy expenditure in the community dwelling older subjects with T2DM.To assess the effects of the three study arms on sarcopenia and frailty measures in the community dwelling older subjects with T2DM.To evaluate whether or not there is a synergistic effect of either medical treatment with empagliflozin or the V-Med diet with the CRT intervention on weight reduction and functional status in community dwelling older subjects with T2DM. This will be done by comparing among each of the interventions alone, and with its combined effect with the other listed co-interventions.

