**Methods:**

One hundred and twenty men and women ≥65 years of age with type 2 diabetes, and low levels of physical activity will be randomized (1:1:1 manner, gender stratified) for 10 weeks to one of 3 parallel arms: CRT consisting of 3 home sessions/week; ad-libitum plant-based Mediterranean diet (limited consumption of eggs, dairy and fish, avoidance of red meat and poultry) or empagliflozin 10 mg/day. After 10 weeks CRT will be added to the empagliflozin and diet arms for an additional 10 weeks. Allocation concealment and blinding of primary outcome assessors will be implemented. Efficacy will be determined by assessment of lean body mass, body weight, frailty and functional status, sarcopenia, HbA1c and quality of life questionnaires. Safety will be evaluated by routine monitoring of adverse events. This study was approved by the Tel-Aviv Sourasky Medical Center Institutional Review Board.

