## Methods/design

### Trial design

This is a single center, open label, parallel group, exploratory clinical trial of CRT for 10 weeks; V-Med diet for 10 weeks and then CRT on top of diet for 10 weeks; empagliflozin 10 mg/day for 10 weeks and then CRT on top of drug therapy for 10 weeks (Fig. 1) in older subjects with T2DM. This trial will be conducted in conformance with Good Clinical Practices (GCP). The duration of the trial will be up to 25 weeks (with up to 8 clinic visits) for each subject. This will include a 1-week screening period (Visit 1 to Visit 2); a 10-week single treatment period (Visit 2 or 3 to Visit 6); a 10-week combination treatment period. Approximately 120 subjects ≥65 years of age with T2DM, diagnosed in accordance with American Diabetes Association guidelines and who meet all enrollment criteria will be randomized. The study will be conducted between May 2018 to September 2020. Information on the trial is disclosed at clinicaltrail.gov (trial no. NCT03560375). The trial will be disclosed according to the requirements of the International Committee of Medical Journal Editors (ICMJE) [32]. This study was approved by the Tel-Aviv Sourasky Medical Center Institutional Review Board. Any important protocol modifications will be reported for approval of the Institutional Review Board.

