#### Assignment of intervention

##### Allocation

At the end of Visit 2- subjects will be randomized at a ratio of 1:1:1 to each study group and stratified based on gender. Randomization will be conducted by a randomization software (computer generated random numbers) [34]. A third party who is not aware of research protocol will allocate patients into the study groups a priori to first recruitment using the randomization software and will create and keep the allocation list. Once recruitment for a particular baseline day and all baseline measurements are finished, a mediator in the IEMH (secretary) will contact the third party to reveal the allocations of the participants recruited and examined so far (allocation concealment).

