### Follow up visits

Subjects will attend the IEMH at TASMC at the following intervals: screening Visit 1, Visit 2- Day 1- baseline day (allocation will be exposed at the end of baseline day; subjects allocated to SGLT-2 arm will meet the physician (RE) for instructions on the drug), Visit 3 Week 0- familiarization of protocol – meeting with the dietitian (AB) for V-Med arm only. Subjects allocated to the CRT arm will meet the physiologist (OK) or a physical instructor (AR) at their homes for familiarization. From familiarization day the 20-week count of the study period will start, and subjects will have an additional five “on site visits” at Week 1 (V-Med arm only; CRT – another visit at home after 1 week from beginning), Week 6 (V-Med arm only), Week 10 (all arms; CRT arm – end of study), Week 16 (V-Med arm only) and Week 20 (SGLTT-2 and V-Med arms) (Table 1).

**Table 1 Tab1:** Study flow chart

	Screening	Baseline day (W0–1)^e^	Familiarization of protocol^b^ (W0–2)	After 1 week (W1)	After 6 weeks (W6)	After 10 weeks^c^ (W10)	After 16 weeks (W16)	After 20 weeks (W20)
On site visit number	1	2	3	4	5	6	7	8
Informed consent	X							
Eligibility criteria form	X							
Medical discharge and list of drugs from primary physician + physical activity confirmation letter	X							
Blood examinations from last 3 months (for eligibility)	X							
Physical examination for vital signs by study physician	X					X		X
Screening blood and urine tests (biochemistry and endocrinology): a) Urine microalbumin, sodium, creatinine, free cortisol) b) TSH, FT4 c) 25 OH vitamin D	X							
Demographic details, questions on health status, lifestyle using MABAT questionnaire	X							
Functional and physical activity questionnaires	X							
Food frequency questionnaire	X							
Guidance about diabetes diary	X							
Drug guidance for drug arm only		X						
Dietary guidance for diet arm only			X	X	X		X	
CRT guidance for CRT arm only			X	X				
CRT guidance for drug and diet arms						X		
Height		X						
Body weight		X				X		X
Body circumferences		X				X		X
Body fat %, lean and muscle mass assessments using BIA method		X				X		X
Resting blood pressure		X				X		X
Resting energy expenditure		X				X		X
24 h blood pressure monitoring		X				X		X
Fasting plasma glucose and HbA1C		X				X		X
Testosterone (T) and bioavailable T		X				X		X
HOMA- Insulin X glucose/23.5		X				X		X
LH, FSH, Estradiol		X				X		X
Diabetes diary (self-monitoring glucose levels, change in drugs)		X				X		X

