Functional and frailty tests	X					X		X
CRT diary (report on training days and performance)			X	X	X	X	X	X
Left of tablets count of drugs						X		X
Adherence to MedD	X					X		X
Food diary – 3 days			X			X		X
Quality of life	X					X		X
Phone calls (adverse events monitoring)			X	X	X	X	X	X
Encouragement using phone calls			X	X	X	X	X	X

^a^Allocation concealment until the end of baseline day – then allocation is introduced both to researcher and the subjects. Subjects allocated to SGLT-2 would meet physician at the end of the day for instruction of the use of the drug and will be supplied with drugs for 20 weeks). Subjects allocated to Diet and CRT groups will make an appointment for the following week (familiarization)

^b^For diet subjects – on site visit and for CRT subjects – familiarization at their homes

^c^At this week CRT group will finish the study and SGLTT-2 and V-Med add CRT on top of their current intervention. Familiarization of the CRT will be performed on the same week.

*Abbreviations*: *BIA* Bioelectrical Impedance Analysis, *BMI* Body Mass Index, *CRT* Circuit Resistance Training, *HbA1c* Hemoglobin A1C, *MedD* Mediterranean Diet

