##### Baseline comparisons

To test differences in continuous variables between the study groups the one-way analysis of variance (ANOVA) test will be performed (or Kruskal–Wallis one-way analysis of variance when normal distribution is rejected). For comparison of dichotomous or categorical variables the Chi square test will be performed.

The primary endpoints (% change in LBM and change in weight) will be analyzed using the analysis of covariance (ANCOVA) after 10 weeks and after 20 weeks (for diet and drug arms only) including several factors and covariates. Table 2 indicates the list of covariates and factors. Table 3 indicates the different outcomes and appropriate statistical method.

**Table 2 Tab2:** List of potential covariates and factors (partial list)

Factor or covariate	Type	Defined as
Treatment	Factor	SGLT2 inhibitor, diet, CRT
GLP1 agonists	Factor	Yes, no
Baseline body weight/ BMI	Covariate	–
HbA1c (%)	Covariate	–
Caloric consumption (Kcal)	Covariate	–
Resting metabolic rate (Kcal)	Covariate	–
Body fat %	Covariate	–
Strength (kg)	Covariate	–
Frailty or sarcopenia status	Factor	Frail or sarcopenic, pre-frail or pre sarcopenic and robust

*Abbreviations*: *BMI* Body Mass Index, *CRT* Circuit Resistance Training, *GLP-1* Glucagon-Like Peptide-1, *HbA1c* Hemoglobin A1C

**Table 3 Tab3:** The different outcomes and appropriate statistical method (partial list)

	Endpoint type	Statistical method
Primary outcome		
Change in body weight (%) from baseline to 10 weeks or to 20 weeks	Continuous	ANCOVA
Change in % lean body mass from baseline to 10 weeks or to 20 weeks	Continuous	ANCOVA
Proportion of participants having lost ≥2.5% at week 10 and 20	Binary	Logistic regression
Secondary outcomes		
Change in waist circumference from baseline to 10 weeks or to 20 weeks	Continuous	ANCOVA
Change in FPG and HB1Ac from baseline to 10 weeks or to 20 weeks	Continuous	ANCOVA
Change in sarcopenia and frailty status (improved vs. not improved; change from one level to the other) at week 10 and 20	Binary	Logistic regression
Change in strength and other functional abilities from baseline to 10 weeks or to 20 weeks	Continuous	ANCOVA
Change in systolic blood pressure from baseline to 10 weeks or to 20 weeks	Continuous	ANCOVA
Change in quality of life (improved vs. not improved; change from one level to the other) at week 10 and 20	Binary	Logistic regression

*Abbreviations*: *ANCOVA* Analysis of Covariance, *FPG* Fasting Plasma Glucose, *HbA1c* Hemoglobin A1C

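### The synergy aim has no concurrent comparison behind it: single treatments are seen only to week 10 and combinations only at week 20, so synergy is not identifiable without untestable assumptions

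*Protocol article*

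**What the plan says.** The protocol article, Specific secondary aims, sets the aim: "To evaluate whether or not there is a synergistic effect of either medical treatment with empagliflozin or the V-Med diet with the CRT intervention", with weight reduction and functional status as the outcomes. It also fixes the method: "This will be done by comparing among each of the interventions alone, and with its combined effect with the other listed co-interventions".

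The design that must support this is described in four places:

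- **Abstract, Methods:** "After 10 weeks CRT will be added to the empagliflozin and diet arms for an additional 10 weeks". Trial design repeats the sequence for the diet arm: "V-Med diet for 10 weeks and then CRT on top of diet for 10 weeks".
- **Follow up visits:** the CRT arm's last visit is given as "Week 10 (all arms; CRT arm – end of study". Footnote c to Table 1 adds: "At this week CRT group will finish the study and SGLTT-2 and V-Med add CRT on top of their current intervention".
- **Allocation:** there is one randomisation, at baseline: "subjects will be randomized at a ratio of 1:1:1 to each study group and stratified based on gender". Nobody is re-randomised at week 10.
- **Statistical methods (under Baseline comparisons):** the primary endpoints are analysed "after 10 weeks and after 20 weeks (for diet and drug arms only").

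The limitations listed in the Discussion do not mention that single and combined treatments are observed at different times.

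**The concern.** Synergy means that a combination does more than its components added together over the same period. Testing it needs the combination and its components at a common time, and something to represent no treatment. Here no arm is on diet, drug or CRT alone at week 20, no arm is on a combination at week 10, and no arm is untreated.

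CRT exposure is matched in length: ten weeks in the CRT arm, and ten weeks as an add-on. Diet or drug exposure (20 weeks against 10) and time in the study are not matched. Whatever diet or drug alone would have done in weeks 10–20, and whatever changes with time in the study, is read as an effect of the combination. For functional outcomes this includes repeat testing. Table 1 schedules these tests at screening, week 10 and week 20, so a week-20 score comes from a third testing and the CRT arm's last score from a second.

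At stake is a secondary conclusion. The trial could report synergy where effects are purely additive, or miss it where it exists.

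**Working it through.** The plan gives no figure for synergy. Its 40 per arm rests on weight at week 10 and does not bear on this point. The check is whether the observed means can yield the interaction at all.

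**Effects (changes from baseline), nine in all:**
- P1, P2: change with time alone in weeks 0–10 and 10–20
- C: effect of ten weeks of CRT, taken as the same whether given early or late (an assumption that favours the plan)
- D1, D2: effect of diet in the first and second ten weeks
- E1, E2: the same for empagliflozin
- D×C, E×C: the two interactions, which are what the aim is about

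**Post-baseline means the design provides, five in all:**

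| Arm and time | Expected change |
|---|---|
| CRT, week 10 | P1 + C |
| Diet, week 10 | P1 + D1 |
| Drug, week 10 | P1 + E1 |
| Diet+CRT, week 20 | P1 + P2 + C + D1 + D2 + D×C |
| Drug+CRT, week 20 | P1 + P2 + C + E1 + E2 + E×C |

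**Step 1: the contrast the aim implies.**
(diet+CRT at week 20) − (diet at week 10) − (CRT at week 10)
= (P1 + P2 + C + D1 + D2 + D×C) − (P1 + D1) − (P1 + C)
= D×C + D2 + (P2 − P1).
The drug contrast is E×C + E2 + (P2 − P1). Comparing the week 10–20 change after adding CRT with the CRT arm's week 0–10 change gives the same expression: (P2 + C + D2 + D×C) − (P1 + C).

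**Step 2: what is estimable.** The five-by-nine system has rank 5.
- With no assumptions, neither D×C nor E×C is estimable.
- With P1 = P2 = 0 (seven effects), both are still not estimable, because D2 and E2 remain.
- With P1 = P2 = 0 and D2 = E2 = 0 (five effects), both are estimable.

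For the contrast in Step 1 taken alone, equal time effects (P1 = P2) together with D2 = 0 would be enough.

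**Step 3: are those assumptions stated?** No. The schedule shows treatment continuing: Table 1 has diet guidance at week 16, and its footnote a has drug supplied for 20 weeks.

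**Step 4: size.** The documents give no value for D2, E2, P1 or P2, so the error cannot be quantified. It is one for one. As an assumed example with zero synergy and no time effect, a further 1 kg loss from drug alone in weeks 10–20 shows as 1 kg of apparent synergy, no further change shows as none, and a 1 kg regain shows as 1 kg of apparent antagonism.

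**Step 5: what stays sound.** At week 20, diet+CRT minus drug+CRT = (D1 + D2 + D×C) − (E1 + E2 + E×C). For the week 10–20 change, the difference is (D2 + D×C) − (E2 + E×C). Time and CRT cancel in both, and both compare randomised arms at the same times. They compare the two regimens; they do not isolate either interaction.

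**The case against.** The strongest reply is that the trial calls itself exploratory, that this is one secondary aim, and that both primary hypotheses use only randomised contrasts: three arms at week 10, then diet+CRT against empagliflozin+CRT at week 20. That stands, and it limits the consequence. It does not rescue the aim, because an exploratory label does not identify an effect that the design cannot separate.

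It can also be said that the aim names no time points or formal contrast, so an invalid synergy statement is an inference about what would follow. That is fair. But the aim does name the comparison, and no later analysis model can supply arms that were not observed.

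A reader might infer more than the documents support:

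- **That synergy can never be addressed.** It can, under a plateau of diet and drug effect and no time effect. The fault is that these assumptions are untestable here and unstated.
- **That season is fully confounded with adding CRT.** The study runs from May 2018 to September 2020 with up to 25 weeks per participant, and allocations are revealed as people are recruited. With staggered entry, weeks 10–20 fall at different times of year and season would largely average out.
- **That a given share of the planned 3.2 kg would be misattributed.** That figure is the assumed week-10 difference between empagliflozin and CRT. It is not a combination or synergy effect, so a share of it measures nothing in this aim.
- **That describing the treatments as given singly and combined is itself wrong.** That phrase describes what participants receive and need not change.

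**Conclusion.** The concern holds in this form: the fourth secondary aim promises an evaluation of synergy that the design can deliver only under two unstated, untestable assumptions, namely no further diet or drug effect after week 10 and no time-in-study effect. Without them, neither the diet-by-CRT nor the drug-by-CRT interaction is estimable (five means, nine effects, rank 5). Assuming away time effects alone is not enough. The resulting error is one for one with the departure, can go in either direction, and cannot be sized from the documents. The algebra rests on additive effects and on CRT having the same ten-week effect early or late; relaxing the latter would add a further unknown.

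The primary hypotheses, the randomised week-10 comparisons and the randomised week-20 comparison of the two combinations are not affected. This is a fault that should be corrected in a secondary aim; it does not threaten the main inferences.

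**What to change.** In Specific secondary aims, replace the synergy wording with two items:

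1. the randomised comparison of diet+CRT with drug+CRT at week 20, and of their change from week 10 to week 20;
2. the within-arm change after CRT is added, labelled descriptive and uncontrolled for time.

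If week-20 values or week 10–20 changes are set beside the CRT arm's week 0–10 results, label that descriptive and state both assumptions (plateau of diet and drug effect, no time effect). Draw no conclusion about synergy, and add the point to the limitations in the Discussion.

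The cost is wording only: no new arm, visit or data. The week-20 comparison of the two combinations is already planned. What is given up is the synergy claim. Following the CRT arm to week 20 would not by itself restore it, because diet-alone and drug-alone values at week 20 would still be missing.

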## Methods/design

### Trial design

This is a single center, open label, parallel group, exploratory clinical trial of CRT for 10 weeks; V-Med diet for 10 weeks and then CRT on top of diet for 10 weeks; empagliflozin 10 mg/day for 10 weeks and then CRT on top of drug therapy for 10 weeks (Fig. 1) in older subjects with T2DM. This trial will be conducted in conformance with Good Clinical Practices (GCP). The duration of the trial will be up to 25 weeks (with up to 8 clinic visits) for each subject. This will include a 1-week screening period (Visit 1 to Visit 2); a 10-week single treatment period (Visit 2 or 3 to Visit 6); a 10-week combination treatment period. Approximately 120 subjects ≥65 years of age with T2DM, diagnosed in accordance with American Diabetes Association guidelines and who meet all enrollment criteria will be randomized. The study will be conducted between May 2018 to September 2020. Information on the trial is disclosed at clinicaltrail.gov (trial no. NCT03560375). The trial will be disclosed according to the requirements of the International Committee of Medical Journal Editors (ICMJE) [32]. This study was approved by the Tel-Aviv Sourasky Medical Center Institutional Review Board. Any important protocol modifications will be reported for approval of the Institutional Review Board.

**Fig. 1 Fig1:**
[figure not shown]
Study flow. Abbreviations: CRT, circuit resistance training; R, randomization; SGLT2, Sodium glucose transport 2; T2DM, type 2 diabetes mellitus; V, visit (on site); V-Med diet, vegeterranean diet

### Study setting

The study will take place at the institute of Endocrinology, Metabolism, and Hypertension (IEMH), Tel-Aviv Sourasky Medical Center (TASMC). We will use a non-probability sampling method composed of patients aged 65 years and older with T2DM visiting the various out-patient clinics in the IEMH (e.g., endocrinology, osteoporosis, diabetes, metabolic syndrome clinics). Further recruitment, if necessary, will be based on retired employees from Tel Aviv municipality and from physician clinics in health maintenance organizations (HMO’s) located in Tel Aviv and its area. Potential participants from all recruitment sources will be shortly informed of the study and will be sent detailed information via e-mail or mail. Their eligibility will be assessed by the study physician (RE) and if willing to participate they will sign an informed consent.

### Eligibility

#### Major inclusion criteria

Subjects who have T2DM in accordance with American Diabetes Association guidelines [33] and:
Are ≥65 years of age (inclusive) on the day of signing the informed consent form (ICF). Subjects may be treated with any anti hyperglycemic agent other than an SGLT-2 inhibitor.Perform ≤2 days a week of any leisure aerobic PA, who are able to walk independently either with or without an assistance device (cane or walker).HbA1C ≥6.5% to ≤8%.

#### Major exclusion criteria

Recent use of steroid agents (< 6 months, replacement therapy is allowed)Uncorrected hypothyroidism [thyroid stimulating hormone (TSH) > 6 mlU/L]Diagnosis of malignancy within the past 5 years except for non-melanoma skin cancerSevere kidney disease (eGFR< 45 cc/ml)Active depressionRecent (≤6 months) or unstable cardiovascular condition; New York Heart Association (NYHA) Class 3 or higher congestive heart failureSubjects with PA limiting pain due to advanced neuropathySubjects performing resistance trainingSubjects who are in active nutritional therapy, changed their diet recently (< 1 month) and/or in a weight-loss program (actively losing weight)Has other severe acute or chronic medical or psychiatric condition or laboratory abnormality that may increase the risk associated with study participation or may interfere with the interpretation of study results.

### Visit 1- screening

All potential eligible subjects will be invited for a screening Visit 1, during which the following information would be obtained:
Informed consent.Physician interview and physical examination.A questionnaire adapted from the national Israeli health and nutrition survey (MABAT) for the older people which includes demographic details, health status, lifestyle as well as descriptive details addressing the functional and physical state.A meeting with the research assistance (AL) (blinded during all study) to assess adherence to the Med-diet, using the PrediMed screener which was recently adopted to Israel.A meeting with the study’s physiologist (OK) comprised of a short interview and frailty and functional assessments.

Screening information from all subjects will be documented and kept in a screening log. Comparisons of baseline characteristics of the included vs. the excluded subjects will be performed at the end of the trial (age, gender, etc.).

### Visit 2- day 1

Subjects that were confirmed as eligible at the end of Visit 1 will be considered as “included subjects”. During Visit 2, subjects will be assigned a 5-digit number (their 5 first ID number’s digits) and the following information will be collected:
Following overnight fasting (12 h) patients will undergo: a) resting metabolic rate (RMR); b) Anthropometric assessment (then food is allowed); c) Fasting blood draw for routine glucose and hormonal profile; d) Blood Pressure (BP) (diastolic and systolic) and pulse measurements; e) eye examination.

